### Statistical methods

An intent-to-treat analysis was planned to compare the relative risk of achieving the primary outcome of linkage to care within 1 month and retention in care at 12 months after HIV testing. The effectiveness of CIS compared to SOC will also be assessed on secondary outcomes including the following: linkage to care within 1 month; retention 12 months after HIV diagnosis; and time from ART eligibility to ART initiation, viral load suppression 12 months after HIV diagnosis, disease progression, and cost-effectiveness. Sub-distribution hazard models, treating death as a competing risk for ART initiation, are to be used to compare the time from eligibility to initiation of ART between participants receiving CIS and SOC, with participants transferring or becoming lost to follow-up after ART eligibility but before initiation censored at their date of transfer or their last recorded visit. Robust sandwich estimates of variance will be used to account for correlation within study units. Sociodemographic and clinical determinants of the primary and secondary outcomes are to be analyzed to examine whether the CIS differentially impacts outcomes within strata by sociodemographic and clinical characteristics (e.g., age, sex, HIV disease stage, CD4+ count, tuberculosis, and pregnancy status). We will conduct covariate-adjusted generalized linear mixed models if important differences are observed between study arms in order to assess the degree to which these differences influence outcomes. For cost-effectiveness analysis, a model will be created to estimate the effect of CIS on health benefits and costs. Differences in life expectancy, quality-adjusted life years, and infections averted between CIS and SOC arms will be estimated using inputs from the study.

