### Study objectives and outcomes

The primary study objective was to evaluate the effectiveness of the CIS compared to SOC on the combined outcome of linkage to HIV care within 1 month of an HIV-positive test and retention in care at 12 months among adults diagnosed with HIV. Linkage to care was defined by at least one visit to HIV clinic with completion of an intake assessment including medical history and physical exam. Retention in care at 12 months after HIV testing was defined as a clinic visit within 90 days prior to the end of the study follow-up period.

The secondary objectives included the evaluation of the effectiveness of CIS compared to SOC with regard to the following: linkage to care within 1 month after testing HIV positive, retention in care at 12 months after testing HIV positive, time to ART eligibility and ART initiation, viral load suppression at 12 months after HIV testing, disease progression, patient acceptability, and cost-effectiveness. Additionally, the effect of sociodemographic and clinical determinants on key study outcomes was to be assessed.

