### Study interventions

#### Standard of care

At study units assigned to the SOC arm of the study, participants were managed as per country guidelines. After testing HIV positive, individuals received post-test counseling and were referred to an HIV clinic using a national referral form that documents the patient’s identification and HIV status. Patients who linked to HIV care received clinical and laboratory assessments for the determination of ART eligibility, including CD4+ count testing and hematology and chemistry tests, and were instructed to return to the clinic in 1 to 2 weeks to receive their results. Upon return, those found eligible for ART initiation received three counseling sessions. The time interval from eligibility determination to ART initiation typically has been 1 to 2 months. All patients were given cotrimoxazole prophylaxis and those not eligible for ART were instructed to return every 3 months to the clinic, while those who initiated ART returned to the clinic every month for 6 months, and then every 3 months if they were stable on treatment. Peer counselors were encouraged to call patients within 7 days of a missed appointment; however, these procedures were often not consistently applied. Condoms and informational materials were available for all patients at HIV clinic visits.

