#### Combination intervention strategy

Participants at study units assigned to the CIS study arm received five evidence-based interventions in addition to SOC interventions. The five interventions include the following: (1) point-of-care CD4+ count testing on the same day as HIV diagnosis, (2) accelerated ART initiation for eligible patients with CD4+ count <350 cells/μL, the prevailing ART eligibility threshold during the conduct of the study, (3) mobile phone appointment reminders, (4) care and prevention bags, and (5) non-cash financial incentives for linkage and retention. Table 2 shows the interventions included in the study, the type of barrier addressed, and the target step in the HIV care continuum. Clinic staff at study units assigned to CIS were trained on each of these interventions and the importance of their provision to all study participants at their site.

**Table 2 Tab2:** Study interventions, type of intervention, and target step in the HIV care continuum

Intervention	Standard of care (SOC)	Combination intervention strategy (CIS)	Type of intervention	Step targeted in HIV care continuum
Point-of-care CD4+ count testing	• Point-of-care CD4 assays available in some primary care clinics and some secondary health centers/hospitals for patients enrolled in HIV care but only used once a patient has linked to care	• Point-of-care CD4 assays at the HIV testing site at the time of HIV testing	Structural and biomedical	Linkage and ART initiation
		• Turnaround time immediate		
	• All clinics have CD4 (Cyflow, FACS Caliber) availability after linkage to HIV care in the clinic or lab			
	• Turnaround time approximately 2 weeks			
Accelerated ART initiation	• ART initiation per national guidelines for patients with CD4 ≤350 cells/μL or WHO stage III/VI	• Accelerated ART initiation for patients with point-of-care CD4 ≤350 cells/μL within 1 week from testing	Structural and biomedical	ART initiation and retention
	• Requires 3 counseling sessions and receipt of baseline lab tests	• 2 counseling sessions (one at the time of HIV testing and another at the first HIV clinic visit), and collection of blood for other baseline lab tests, but ART initiation prior to return of results for patients who do not meet the criteria for waiting for receipt of lab results prior to ART initiation		
	• Initiation 2 weeks–1 month from testing			

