*Point-of-care CD4+ count testing*. Each participant at sites randomized to CIS received a point-of-care CD4+ count test immediately after testing HIV positive. The CD4+ count test was conducted by the study staff and took approximately 20 min to process. CD4+ count results and their implications were provided to the participant, and a copy was placed in the patient’s national referral form for HIV care. Regardless of the CD4+ count result, all participants were encouraged to link to HIV care within 1 week of receiving the results.*Accelerated ART initiation for eligible participants*. This intervention streamlined the preparatory procedures required for ART initiation by consolidating the ART counseling sessions into two sessions, as compared to three in standard of care, in order to enable ART initiation within 1 week of diagnosis. At sites assigned to CIS, the first ART preparatory counseling session was given at the time of receiving the point-of-care CD4+ count result at the HIV test site. The second session was given by the clinic staff at the HIV care site, at the first visit upon linkage to care by the participant. Clinic staff collected samples for the required baseline laboratory tests per national guidelines. Clinicians were encouraged to initiate ART at this first care visit, rather than awaiting the results of these laboratory tests in participants with no comorbid conditions. For participants that needed further counseling and/or clinical assessments, initiation of ART was done at the discretion of the clinician. Participants who initiated ART received a 2-week supply of medications per national guidelines. Baseline laboratory results were reviewed by the study staff with the clinic staff soon after availability, and if any abnormality was noted, participants were contacted to return to the clinic. After initiating ART, all follow-up visits followed national guidelines, similar to the standard of care procedures.*Mobile phone appointment reminders*. All participants at sites assigned to CIS received appointment reminders via mobile phone SMS, or voice message reminders for illiterate participants, to encourage linkage to care and completion of scheduled clinic visits. Reminders were sent to the participant’s phone or on a friend or relative’s phone per participant preference. The reminders did not refer to HIV or reveal any personal information. An example message is: “Good day – This is a reminder about your visit at [health facility] tomorrow. We look forward to seeing you then*.*” SMS were sent from a central server 1 day prior to scheduled clinic visit date for all participants. For participants who missed appointments, a text message was sent within 7 days to encourage the participant to return to the clinic.*Basic care and prevention package*. All participants at sites assigned to CIS received a package of commodities and informational materials upon linkage to care and once every 3 months thereafter during the study period. This package was designed to offer an opportunity to have further counseling on HIV care through provision of commodities that were deemed of value by the patients. Commodities in the package included condoms, a pillbox, soap, toothbrush and paste, cotrimoxazole tablets, and an appointment calendar. The health counseling that accompanied each package used existing national health information and educational materials (i.e., pamphlets, pictures) that focused on medication adherence, family planning, tuberculosis screening and cough hygiene, and nutrition.*Non-cash financial incentive (FI)*. All participants at sites assigned to CIS who linked to care within 1 month of HIV testing and those who completed HIV care clinic visits at 6 and 12 months after HIV testing received a non-cash FI in the form of prepaid mobile phone airtime vouchers. Each FI consisted of 80 Swaziland Emalangeni ($8–10), an amount selected based on the estimated cost of traveling to the clinic and with consultation with key stakeholders in the country.

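### The only ART-initiation comparison described starts its clock at eligibility, which is established at testing in CIS but only after linkage in SOC, so the arms differ in time zero and in who is at risk

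*Protocol article*

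**What the plan says.** Statistical methods in the Protocol article names the ART outcome among those on which the effectiveness of CIS against SOC is assessed. It plans sub-distribution hazard models, with death as a competing risk, that "are to be used to compare the time from eligibility to initiation of ART between participants receiving CIS and SOC". Participants transferring or "becoming lost to follow-up after ART eligibility but before initiation censored at their date of transfer or their last recorded visit".

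The point at which eligibility becomes known differs by arm:

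- **CIS** (Combination intervention strategy): "Each participant at sites randomized to CIS received a point-of-care CD4+ count test immediately after testing HIV positive". This happens at the testing site, before linkage.
- **SOC** (Standard of care): "Patients who linked to HIV care received clinical and laboratory assessments for the determination of ART eligibility", with a return visit 1 to 2 weeks later for results. Table 2 adds that point-of-care CD4, where an SOC clinic has it, is "only used once a patient has linked to care".

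Study objectives and outcomes words the objective differently, as "time to ART eligibility and ART initiation", and gives no time origin. No ART comparison timed from the HIV test is described.

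**The concern.** A between-arm comparison inherits the protection of randomisation only if everyone randomised enters it from an origin that the intervention cannot move. Neither condition is met here. CIS brings the origin forward to the day of testing. In SOC a participant has to link before there is any origin at all. Linkage is half of the primary outcome, so SOC entry to the risk set is conditional on something CIS is meant to change.

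Point-of-care CD4 and accelerated ART are two of the five components, and Table 2 lists ART initiation among the steps that each targets. Table 2 also times the CIS goal from testing. A clock that starts at eligibility cannot show the benefit of reaching eligibility sooner or in more people. As this is the only ART-initiation comparison described, readers would take its hazard ratio as the effect of CIS on starting treatment.

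**Working it through.** The article gives no power or expected effect for the ART outcome, so there is no planned figure to reproduce. The 50% linkage figure is the plan's own working assumption: 0.50 × 0.70 = 0.35, the SOC rate used for the sample size.

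**Inputs from the document.** SOC linkage within 1 month is 50%. Results come 1 to 2 weeks after the assessment (taken as 7–14 days). SOC eligibility to ART takes 1 to 2 months (taken as 30–60 days).

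**Assumptions not in the document.** Linkers link evenly over days 0–30, 85% of linkers start ART, there are no deaths, and everyone is CD4-eligible at testing.

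**Step 1: who enters the risk set.** In SOC, 50% of eligible people enter (40% to 70% if linkage is varied over that range). In CIS, 100% have an eligibility result.

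**Step 2: when the clock starts.** In SOC linkers, the mean is 15 days to link + 10.5 days to results = 25.5 days after testing (range 0 + 7 = 7 to 30 + 14 = 44 days). In CIS it is day 0.

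**Step 3: a null case.** Give both arms the same 50% linkage and the same test-to-ART delays. The only difference is that CIS has its CD4 recorded at testing. Mean time from test to ART among starters is 15 + 10.5 + 45 = 70.5 days in both arms. The eligibility clock records 45 days in SOC and 70.5 in CIS.

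| ART by day 90 (simulated) | SOC | CIS |
|---|---|---|
| From HIV test, everyone included | 40% | 40% |
| From eligibility, CIS non-linkers kept at risk | 85% | 40% |
| From eligibility, CIS non-linkers censored at day 0 | 85% | 0.397 / 0.50 = about 79% |

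The corresponding hazard ratios (CIS to SOC) are about 0.17 with non-linkers kept at risk and about 0.42 to 0.44 with day-0 censoring. A ratio of 1 would be correct. The first reflects both the different populations and the different clocks. The second reflects the clocks alone.

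**Step 4: a case with a real CIS benefit.** Assume CIS linkage of 70%, initiation after linkage of 80% in SOC and 90% in CIS, and ART at the first CIS clinic visit. Among all eligible people tested, 0.50 × 0.80 = 40% of SOC and 0.70 × 0.90 = 63% of CIS start ART, a ratio of 1.58. With a 30–60 day SOC interval, the eligibility-clock hazard ratio is about 1.2 with CIS non-linkers kept at risk and about 3.5 to 3.9 with them censored at day 0. If the SOC interval is only 0–30 days and non-linkers stay at risk, it falls below 1 (0.43 to 0.85 over SOC initiation of 70–90% and CIS initiation of 80–90%).

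The same benefit can thus appear as harm, a small gain or a large gain, according to censoring and delay.

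The SOC delay that drives this is itself inconsistent in the document. Standard of care gives 1 to 2 months from eligibility to ART, while Table 2 gives 2 weeks to 1 month from testing. Those two passages must be reconciled.

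**The case against.** Several points on the other side have force.

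- **The outcome is secondary.** This stands. The primary outcome is timed from HIV testing, as are linkage, retention and viral suppression.
- **The censoring rule may remove CIS non-linkers.** Their last recorded visit is plausibly the testing visit. That would narrow the difference in populations, but it makes censoring depend on non-linkage and leaves the clocks apart, as the null case shows.
- **A full protocol or SAP may define the eligibility date and the entry rule.** It may. But the article already fixes the origin, the model, the competing event and the censoring, and the flaw lies in that origin.
- **Eligibility-to-ART is a meaningful measure of the accelerated-ART component.** It is, and it is worth reporting. It is not a randomised comparison.
- **Not every CIS participant becomes eligible on day 0.** WHO stage also confers eligibility, and a CD4 count can fall later. The point concerns CD4 eligibility at baseline.

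A reader might infer that the planned analysis is bound to understate or reverse a CIS benefit. The document does not support that. A ratio of end-of-follow-up proportions, 63% / 80% = 0.79, suggests it, but ignores event timing and the stated censoring. With the 30–60 day interval the same inputs give a hazard ratio above 1. A reader might also infer a breach of the plan's intent-to-treat commitment, but the article attaches that term to the primary outcome only.

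**Conclusion.** The point holds for this secondary outcome and should be fixed. As an estimate of the effect of CIS on ART initiation, the described contrast is biased, because both its time origin and entry to its SOC risk set depend on arm and on linkage. This follows from the text and needs no assumed rates.

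The size does rest on assumptions. In the null case, with identical test-to-ART times, CIS shows a spurious disadvantage under either handling of non-linkers (85% against 40%, or against about 79%, by day 90). Once CIS really changes linkage and delays, the size and direction of the net distortion depend on how CIS non-linkers are censored and on the actual delays. Neither can be derived from the document.

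**What to change.** 1. Make the between-arm ART comparison time from the HIV-positive test to ART initiation, in all enrolled participants in both arms, with death as the competing event and follow-up to 12 months. Participants who never link should stay in the risk set as not having started. If the last-visit censoring rule is carried over, they could drop out at the testing visit.
2. Keep time from eligibility to initiation as a supporting process measure, labelled as not a randomised comparison.
3. Use one definition, with its origin, in both Study objectives and outcomes and Statistical methods.

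Suggested wording: *Time from the HIV-positive test to ART initiation will be compared between arms in all enrolled participants over 12 months, with death as a competing event and variance estimates robust to clustering by study unit. Time from eligibility to initiation will be reported as a process measure and not as a randomised comparison.*

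**Cost.** The change is to the analysis only, and Trial status says that 12-month procedures and record abstraction were still under way. The estimate will include people not yet eligible for ART, which lowers absolute initiation in both arms. Restricting to those eligible at testing cannot be done equally, because SOC has no CD4 at that point. The analysis also needs the ART start date from chart abstraction, which Data collection implies but does not name, so its availability should be confirmed.

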## Methods

### Study design

Link4Health is a cluster site-randomized trial. The unit of randomization is a network of secondary HIV clinics paired with an affiliated primary-level HIV clinic, which is referred to as a study unit (Fig. 1). The study unit reflects the ongoing process of decentralization of HIV care from larger facilities to primary-level facilities in Swaziland [38]. Ten study units were selected from the 11 existing secondary facilities in the country. The largest primary-level facility affiliated with each selected secondary facility was selected based on HIV program size (i.e., number of HIV patients in follow-up at the site based on 18-month historic data, with special attention given to the most recent 6 months). Study units were randomized to the combination intervention strategy (CIS) or standard of care (SOC) strategy using matched-pair randomization balanced by the following factors: facility location (rural, urban), expected number of adults enrolled in HIV care at each facility per month, and implementing partner supporting the facility (Table 1). Sites within matched pairs were randomized to receive either CIS or SOC by generating a random integer using Microsoft Excel, taking the alphabetically first site name if the random integer drawn was 1, and the alphabetically second site name if the random integer drawn was 2.

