### Sample size and power calculations

We estimated that 35 % of participants in the SOC study arm would achieve the combined primary outcome (assuming 50 % link to HIV care within 1 month and 70 % of those linking within 1 month are retained 12 months after study enrollment). We estimated that approximately 2750 adults would be eligible for study enrollment based on historic testing volume, the proportion testing HIV positive at the study units from 2010 to 2011. Assuming 80 % of eligible individuals consent to enroll in the study, we estimated an average enrollment of 220 participants per study unit or 2200 in total with 1100 per study arm.

With this sample size and five study units per study arm, we estimated the minimum difference in the primary outcome we could detect with 80 % power using a two-sided Farrington and Manning Likelihood Score Test [19], assuming an interclass correlation coefficient of 0.05. Estimates were made using the Power and Sample Size (Pass 8.0) software program. With these assumptions, the study has 80 % power to detect an absolute increase of 20 % or more in the CIS versus SOC arm on the primary outcome of linkage within 1 month and retention at 12 months.

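### With only ten study units, robust sandwich variance in its ordinary form gives a nominal 5% test about 12% type I error (equal, effectively unmatched units); a small-sample method and t reference should be fixed

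*Protocol article*

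**What the plan says.** Statistical methods plans an intent-to-treat comparison of the relative risk of the primary outcome. It then describes sub-distribution hazard models for time from ART eligibility to initiation, and directly after them states: "Robust sandwich estimates of variance will be used to account for correlation within study units". No small-sample correction, reference distribution or degrees of freedom is given. Generalized linear mixed models also appear, but only as a covariate-adjusted analysis if the arms turn out to differ importantly.

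The number of clusters is fixed elsewhere. Study design says "Ten study units were selected from the 11 existing secondary facilities in the country" and describes matched-pair randomization; Table 1 lists the five pairs. Sample size and power calculations starts from "With this sample size and five study units per study arm", with "we estimated an average enrollment of 220 participants per study unit or 2200 in total with 1100 per study arm". It gives the other planning values as "assuming an interclass correlation coefficient of 0.05" and "35 % of participants in the SOC study arm would achieve the combined primary outcome", and claims "80 % power to detect an absolute increase of 20 % or more in the CIS versus SOC arm" using a "two-sided Farrington and Manning Likelihood Score Test". No alpha is stated.

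**The concern.** The sandwich estimator is consistent as the number of clusters grows, not as the number of participants grows. With five units per arm, the 1100 participants per arm do not help. Two separate errors arise if it is used in its ordinary form:

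- The variance is biased downward, because each unit's residual is taken around an arm mean that the unit itself helped to determine.
- A normal critical value treats the variance as known, although it is estimated from about 8 degrees of freedom.

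Unless strong matching happens to offset them, both make intervals too narrow and p-values too small. If the method also applies to the primary relative risk, an ineffective strategy could be declared effective about twice as often as intended, in a trial meant to inform HIV service policy. The time-to-ART comparison, to which the sentence clearly applies, has the same problem.

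**Working it through.** **Inputs from the protocol article:** ten units, k = 5 per arm; average 220 per unit, 1100 per arm; ICC 0.05; control rate 0.35; difference 0.20; two-sided test. **Assumed:** alpha 0.05. **Not given, so varied:** spread of unit sizes (CV) and within-pair correlation.

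**1. The plan's own power figure.**
- Design effect = 1 + (220 − 1) × 0.05 = 11.95.
- Effective sample size per arm = 1100 / 11.95 = 92.05.
- Standard error of the difference = √[(0.35 × 0.65 + 0.55 × 0.45) / 92.05] = 0.0718.
- Normal-reference power = Φ(0.20 / 0.0718 − 1.96) = 79.5% (78.3% with pooled variance).

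The stated 80% therefore reproduces with a normal reference. With a t reference on 8 df, the same inputs give 68.5% power, and the difference detectable with 80% power is 22.9 points.

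**2. Type I error, equal and effectively unmatched units.** With k equal units per arm, the uncorrected sandwich variance averages (k − 1)/k = 4/5 of the true variance. The test statistic then behaves as t(8) × √(5/4).

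| Variance | Reference | Type I error |
|---|---|---|
| Uncorrected | normal | P(\|t8\| > 1.96 × √0.8 = 1.753) = 11.8% |
| Uncorrected | t(8) | P(\|t8\| > 2.306 × √0.8 = 2.063) = 7.3% |
| Factor 10/9 only | normal | 10.2% |
| Factor 5/4 (unbiased) | normal | P(\|t8\| > 1.96) = 8.6% |
| Factor 5/4 (unbiased) | t(8) | 5.0% |

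So the 12% is the joint effect of variance bias and the normal reference. The familiar G/(G − 1) = 10/9 factor does little.

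**3. Simulation.** For a log relative risk with cluster sandwich and normal reference (beta-binomial outcomes, rate 0.35, ICC 0.05), type I error was 11.7%. It was 11.4 to 11.8% across ICC 0.01 to 0.10 and rates 0.35 to 0.45, and the mean standard error was about 0.86 of the true one. A censored exponential rate-ratio model, used as a proxy for the time-to-event analysis, gave 10.8 to 11.6%.

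**4. Dependence on what the article does not give** (uncorrected sandwich, normal reference, pairing ignored):

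| Within-pair correlation | Equal sizes | Size CV 0.5 |
|---|---|---|
| 0 | about 11 to 12% | about 14% |
| 0.25 | about 8% | about 10.6% |
| 0.5 | about 5% | about 7.6% |

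At pair correlation 0.75 with equal sizes it falls to about 2%. With no pair correlation and a size CV of 0.65 it rises to 16 to 17%.

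**5. Interval width.** The valid unpaired interval, relative to the uncorrected one, is (2.306 / 1.960) × √(5/4) = 1.315 times as wide.

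**The case against.** The strongest reply is that the article never says the sandwich is uncorrected and never names a normal reference. Mancl-DeRouen and Kauermann-Carroll estimators are themselves robust sandwich estimators, so the sentence is compatible with the fix, and the full protocol or SAP, not shown, may contain it. This stands as a limit on certainty: a reader might infer that the plan has committed to an invalid test, and the document does not establish that. It does choose a method that fails in its usual form at ten clusters. Its power figure also reproduces only with a normal reference, which suggests that the small number of units was not allowed for.

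Three further limits stand:

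- **Scope.** The sentence follows a secondary analysis. A reader might take inflated error in the primary comparison as stated fact; it is the natural reading, but not an explicit one. If the sentence does not reach the primary outcome, the article names no method for clustering in that main comparison.
- **Matching.** A reader might take 12% as the trial's error rate. If matching worked well and the analysis ignores it, the error may be nominal or even conservative. That would be two faults offsetting each other by chance, and at pair correlation 0.5 the offset is already incomplete when unit sizes vary (about 7.6% at CV 0.5).
- **Cause.** Standard errors that are too small do not by themselves produce 12%; they produce 7.3%.

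It can also be said that an unpaired 8-df test ignores the design. That is correct: its true size is about 3% at pair correlation 0.25 and 1.6% at 0.5. The fix therefore has to address pairing.

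**Conclusion.** The concern holds in conditional form. Robust sandwich variance with five units per arm, applied in its ordinary form, has about 12% type I error at a nominal 5% level when units are equal in size and effectively unmatched. Under the other assumptions examined it runs from about 14% (size CV 0.5, no pair correlation), through 8 to 11% (pair correlation 0.25), to 5 to 7.6% (pair correlation 0.5).

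This rests on an inferred absence of correction, an inferred normal reference, an assumed alpha of 0.05, and assumed values for size variation and pair correlation. It applies directly to the time-to-ART models and, on the natural reading, to the primary relative risk. What the document supports is that the stated method is unsuitable for ten units unless a small-sample form is specified.

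**What to change.** Amend Statistical methods before outcome data are analysed; by the Trial status section, follow-up is still being completed.

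- **Primary relative risk.** State that the clustering method covers it. Use a small-sample-corrected sandwich (such as Mancl-DeRouen or Kauermann-Carroll) with a t reference on about 8 df, or a t-test on the ten unit proportions. In simulations over size CV 0 to 0.65 and pair correlation 0 to 0.5, type I error was 1.7 to 5.2% for the unit-level t-test, 1.0 to 4.1% for Mancl-DeRouen with t(8), and at most 7.0% for Kauermann-Carroll with t(8). Either of the first two is safer if unit sizes differ greatly. Simply multiplying the variance by 5/4 is not enough in that case: with t(8) it gives 5.7 to 6.3% at CV 0.4 and 7.8 to 8.3% at CV 0.65.
- **Pairing.** Prespecify a paired analysis (4 df, holds 5% at any pair correlation) or an unpaired one (8 df, valid but conservative if matching worked).
- **Sub-distribution hazard models.** Use a leave-one-unit-out jackknife variance with the same t reference.
- **Permutation.** Do not rely on a within-pair permutation test alone: 2⁵ = 32 allocations give a minimum two-sided p of 2/32 = 0.0625.
- **Power.** Restate it on the chosen basis.

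The change needs no further participants or visits. It does cost precision: intervals are about 1.3 times as wide, and power at 20 points is about 68% (unmatched, 8 df), with 22.9 points needed for 80%. A paired 4-df analysis with no gain from matching has about 56% power and needs 26.7 points; effective matching would recover some of this. Enrollment is complete, so the loss cannot be made up by recruiting more.
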